### Time points

The phase II study timeline, summarized in Figure 3, begins with the start of transition and concomitant entry (E) into the study at time point T0 (baseline), and proceeds with a 12-month assessment at time point T1 and a 24-month assessment at time point T2. At T0 we will collect data for each group about each patient’s expectations for the transition, health status, time since transplantation, quality of life, satisfaction with medical care, therapy, adaptation to the disease, healthcare utilization, social environment, education, gender, age, and number of siblings. At T1, both groups will be evaluated for the transition planned, health status, quality of life, satisfaction with medical care, healthcare utilization, therapy system, and adherence. The intervention group will also be asked additional questions at T1 regarding their experience with the smartphone and app and how well they have adopted the program. After the T1 evaluation, each patient will be transferred to their respective adult care nephrologist. The following variables will be assessed at T2: evaluation of the transition, health status, quality of life, satisfaction with medical care, healthcare utilization, therapy system, education, employment, relationship status, and adherence.

**Figure 3 Fig3:**
[figure not shown]
**Structure of the intervention study (Phase II).**

Baseline data will be documented once, retrospectively. The course of immunosuppressive agent levels and eGFR, the number of acute rejection reactions (examined every four to eight weeks), and eventually the detection of donor-specific antibodies if evaluated by the nephrologist, will be recorded as surrogate parameters of therapy adherence. This diagnostic schedule is in accordance with standard German healthcare and would be followed regardless of participation in the study. No blood samples will be collected in addition to those collected in the normal course of care. Necessary data will be extracted retrospectively from patient files and added to the electronic clinical record file during the study.

### Protection against bias

Firstly, this is a prospective, randomized, intervention study. Secondly, patients are being assigned to groups by block randomization with a variable block length. Randomization will be performed for the most important prognostic factors, namely center, gender, and time after transplantation (less than five years or five years or more). The stratification for center will ensure that for both centers with and without experience in transition patients will be enrolled randomly to both groups. In this way, it will also ensure that the different approaches used in adult centers after transition will be distributed equally in both groups. Thirdly, the costs for the Berliner TransitionsProgramm are being absorbed for those patients whose health insurance company refuses to cover the costs. For all other patients, the costs will be regulated by health insurance.

### Study endpoints

The long-term goal of this work is to improve adherence through a controlled transition process. The primary outcome variable of the study is therapy adherence, as indicated by individual variability in immunosuppressive agent levels. Immunosuppressive agent levels will be recorded at all regular follow-up examinations (every four to eight weeks). A coefficient of variation (%) will be calculated for each patient based on these examination data. These coefficient values will serve as a surrogate parameter for patient adherence. The individual coefficient of variation (%) for immunosuppressive agent levels is the endpoint of choice for this field of research [15].

The secondary endpoints of the study are change in pre- and post-transfer eGFR (using the Schwartz 2009 formula [16], Modification of Diet in Renal Disease formula [17], and cystatin-C levels), serum creatinine levels, transplant survival, patient survival, acute rejection reactions (presence of donor-specific antibodies and chronic-humoral rejection), transplant loss, death, patient satisfaction, healthcare utilization, and patients’ self-reported quality of life and social integration.

### Statistical analysis

The coefficients of variation (%) for immunosuppressive agent levels will be analyzed by analysis of covariance, with adjustment for immunosuppressive agent level at T0 and all stratification variables considered in the randomization, such that the analysis of covariance can be used to determine group differences. [18] Least squares means will be calculated for each group and the difference between the group means will be reported with a two-sided 95% confidence interval (CI). If the upper limit of the CI for the difference between the adjusted means (transition minus standard) for the therapy effect is less than 0, then lower variability in immunosuppressive agent levels and thus better adherence to therapy due to the new transition model is therefore proved. Sensitivity analyses will be carried out using multivariate regression models with consideration of additional prognostic factors (modeling after stepwise variable selection). Secondary dichotomous endpoints (such as transplant loss) will be assessed with multivariate logistic regression models.

All patients included in the study (intention-to-treat population) will be considered in the primary and secondary analyses described above. For patients who suffer a transplant loss, the immunosuppressive agent levels measured before the loss will be used. Using a conservative approach, patients with fewer than three immunosuppressive agent level datum points will be coded with the largest coefficient of variation (%) in their respective therapy group. The study began recruiting patients as from 1 April 2014 (pre-screening).

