## Methods/Design

### Subjects

The study was approved by the research ethics committee of the Hannover Medical School (approval number: 6660). Informed consent will be obtained from the adolescent patients, as well as from their parents. The study cohort will include male and female patients who have undergone a kidney transplant who were between 16 and 22-years-old at study enrollment. There is a huge variation in age at transition in Germany; several centers make the transfer at 18 years whilst others do not transfer until the age of 22. For inclusion the patient must be: at least 14 months away from expected transfer to adult medical care, at least three months post-transplantation, capable of operating a smartphone, and able to provide informed consent. Exclusion criteria are: signs of acute transplant rejection or indications of a need for dialysis in the foreseeable future (since transplant survival is a study outcome variable), as well as mental incapacity (since it may prevent complete and independent use of the apps). Patients will be randomized into two groups: an intervention group that receives case management by the Berliner TransitionsProgramm, which is supported by a smartphone (Samsung Galaxy Y, Samsung, Seoul, South Korea) with two apps; and a control group transferred according to the established protocols of the center. There are centers in Germany which already practice some kind of transition management, however, no center actually uses smartphone apps or case management. Our interventions can also therefore improve outcome in centers that already practice active transition. Because of the center-based stratification used in this study, patients from German centers actually performing transition will be distributed equally amongst both groups.

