### Sample size calculation

We first estimated the likely therapy adherence rate based on a small group of patients on immunosuppressive therapy. Data from Hannover Medical School showed that among six selected patients, three showed very good compliance, with a mean coefficient of variation (%) of 0.13 (±0.03), whereas poor compliance was observed in the three remaining patients, with an average coefficient of variation (%) of 0.5 (±0.03). These values were taken as roughly predictive of the variance we would observe in our study. We will receive additional data from phase I on which to base the sample size assumptions. Assuming a population of 50% with very good compliance, 25% with average compliance, and 25% with poor compliance, we simulated a mixed distribution with the statistical values above and calculated an average coefficient of variation (%) of 0.26, with a standard deviation of 0.15. Our expectation is that the intervention will increase the ratio of patients with good compliance. For that reason we assumed the following positively shifted distribution (%) for the intervention group: 70:30:0 of very good:average:poor compliance. This distribution corresponds to a coefficient of variation (%) of 0.181 with the same standard deviation of 0.15. Assuming a two-sided type I error of 5%, a Student’s two-sample t-test will have 80% power under the planning assumptions if n = 57 patients per group are randomized. Hence, a total of 114 patients must be recruited for this trial. We supposed a negligible dropout rate since it is critical that transplant patients receive ongoing care and attend their treatment centers regularly. In addition, we believe that providing free smartphones will increase adherence. In the unexpected case of too many dropouts, we will extend the recruitment phase to ensure sufficient patients are included in the trial throughout the complete follow-up period.

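### The primary ANCOVA pools CVs over unspecified immunosuppressive agents and adjusts for a raw T0 level without a term for the agent; the test stays valid, but precision may be lost at little saving

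*Protocol article*

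**What the plan says.** - **Endpoint.** Under Study endpoints, levels from all regular follow-up examinations are reduced to one number per patient: "A coefficient of variation (%) will be calculated for each patient based on these examination data". The section does not say which agent's levels are meant.
- **Eligibility.** The criteria under Subjects concern age, timing, ability to take part and graft status, for example "at least 14 months away from expected transfer to adult medical care, at least three months post-transplantation". None restricts the agent.
- **Randomisation factors.** Protection against bias lists them: "namely center, gender, and time after transplantation (less than five years or five years or more". Agent is not among them.
- **Primary model.** Statistical analysis specifies "analysis of covariance, with adjustment for immunosuppressive agent level at T0 and all stratification variables considered in the randomization". The success rule rests on the confidence interval from this model.
- **Baseline data.** Time points includes therapy among the items collected at T0: "quality of life, satisfaction with medical care, therapy, adaptation to the disease, healthcare utilization".
- **Sensitivity models.** "Sensitivity analyses will be carried out using multivariate regression models with consideration of additional prognostic factors (modeling after stepwise variable selection". Agent is not named there.

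**The concern.** A CV is free of units, so it can be calculated for any drug. That alone does not make CVs of different drugs exchangeable: two fully adherent patients on different agents may have different usual variability. If so, a model without the agent leaves some of that spread in the residual. A chance excess of one agent in one arm would then move the adherence contrast for a reason other than adherence.

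The covariate that is in the model makes the omission more noticeable. A T0 level is the concentration of a particular drug. Put into one ANCOVA with a single slope over unspecified agents, it mixes two things: which drug the patient takes, and how high that patient's level is for that drug. Naming the agent separates them.

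At stake is the precision of a trial planned with little slack: 57 patients per group and no allowance for dropout.

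**Working it through.** **Inputs from the article (Sample size calculation).** Control arm: "calculated an average coefficient of variation (%) of 0.26, with a standard deviation of 0.15". Intervention mean 0.181 with the same SD. The difference is 0.26 - 0.181 = 0.079. Two-sided 5%, 80% power, 57 per group.

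**Inputs assumed.** The article gives neither an agent mix nor a CV by agent. I take two agents, with share p = 0.2 to 0.4 on the second and a difference in mean CV of D = 0.05 to 0.15.

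**Step 1: reproduce the plan's figure.** By normal approximation, n = 2 x (1.960 + 0.842)^2 x 0.15^2 / 0.079^2 = 56.6, so 57 per group, as stated. By the exact t-test n = 57.6, and power at 57 per group is 79.6%. The sample size is not in error on this point.

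**Step 2: variance due to agent.** Between-agent variance is p(1-p)D^2. For p = 0.3 and D = 0.10 this is 0.21 x 0.01 = 0.0021. Against 0.15^2 = 0.0225 it is 9.3%.

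**Step 3: gain from adjustment, if 0.15 already contains agent differences.** Residual SD = sqrt(0.0225 - p(1-p)D^2). Power is for the t-test at 57 per group and ignores the one or two degrees of freedom spent.

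| p | D | Residual SD | Power |
|---|---|---|---|
| any | 0 | 0.150 | 79.6% |
| 0.2 | 0.05 | 0.149 | 80.3% |
| 0.4 | 0.05 | 0.148 | 80.7% |
| 0.3 | 0.10 | 0.143 | 83.3% |
| 0.2 | 0.15 | 0.137 | 86.0% |
| 0.4 | 0.15 | 0.131 | 89.2% |

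The gain is about 1 point or less at D = 0.05, 3 to 4 points in the middle case, and up to about 10 points at the far end.

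**Step 4: the same, if 0.15 is the SD within one agent.** Ignoring the agent then inflates the SD to sqrt(0.0225 + p(1-p)D^2). For p = 0.3 and D = 0.10 this is 0.157, and power falls to 76.0%.

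**Step 5: what the planned covariates may already remove.** Suppose the second agent's levels are R times those of the first, and levels spread by a fraction s of the mean within each agent (both assumed). A linear T0 term then takes up this share of the agent variance:

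p(1-p)(R-1)^2 / [p(1-p)(R-1)^2 + s^2((1-p) + pR^2)]

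For p = 0.3:

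- R = 2, s = 0.5: 0.21 / (0.21 + 0.25 x 1.9) = 31%.
- R = 20, s = 0.3: 75.81 / (75.81 + 0.09 x 120.7) = 87%.
- R = 1: none.

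In the middle case, 31% absorption means power is already 80.7% before the agent is added, so the gain to 83.3% is 2.6 points. With 87% absorption power is already 82.9%, and the gain is about 0.5 points. Centre adjustment removes a further part if agent choice follows centre practice. The powers in Step 3 are therefore upper bounds.

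**Step 6: chance imbalance.** The SD of the between-arm difference in agent share is sqrt(2p(1-p)/57), which is 0.086 at p = 0.3. Multiplied by D = 0.10 it shifts the contrast by 0.009 at one SD and 0.017 at 1.96 SD. Over the assumed range the 1.96-SD shift runs from 0.007 to 0.027, against a planned effect of 0.079. The standard error of the contrast is 0.15 x sqrt(2/57) = 0.028, so a one-SD imbalance in the middle case is about 0.3 standard errors.

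**The case against.** The strongest reply is that the premise is not in the document. Nothing states that several agents are in use in material shares, or that their CVs differ under full adherence. That stands, and it is why the point is conditional and its size cannot be derived from the article.

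Second, an omitted covariate is not an error in a randomised trial. A reader might infer that the treatment comparison is biased or the type I error inflated. The document does not support this: randomisation protects both, and the confidence interval covers chance imbalance on average.

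Third, a reader might infer that all agent differences end up in the error term. That is also too strong. The T0 level can stand in partly for the agent, as Step 5 shows, and centre is in the model. A baseline CV, if it replaced the T0 level, would carry some of the agent's usual variability too. So this point overlaps with the choice of baseline covariate.

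Fourth, an article condenses, and the full protocol or analysis plan may define which agent's levels form the CV. That is fair for the definition. The covariates, however, are not left open: the article states the set and ties its success rule to that model. The stepwise sensitivity models could pick up the agent, but it is not named there, and those models do not carry the conclusion.

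Finally, the article lists only therapy at T0. That the agent is on record is a short inference, supported by the fact that a T0 level must belong to some agent.

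**Conclusion.** The point holds as one of precision. The primary model pools CVs over unspecified agents, adjusts for a concentration without saying of what, and omits a baseline factor that the trial appears to collect already. If agents differ in usual CV, part of that difference may stay in the residual and in chance imbalance.

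The size rests on assumed inputs: a two-agent mix with 20-40% on the second agent, a CV difference of 0.05-0.15, and the planning SD of 0.15 taken to include agent differences. On these, power rises from about 80% to at most 80-89%, with 83% in the middle case. The upper end needs a CV difference of about twice the planned treatment effect (0.15 / 0.079 = 1.9). If nearly all patients take one agent, or the agents' CVs are alike, the gain is negligible. The change is worth making because it costs little and gives the T0 level a common meaning, not because the planned test is invalid.

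**What to change.** Before outcome data are analysed, name the agent whose levels form each patient's CV, and enter that agent as taken at baseline as a factor in the primary ANCOVA, with rare agents pooled into one category. If the T0 level is kept as a covariate, standardise it within agent.

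Do not limit the CV to levels of the agent taken at T0. A patient who switches would lose all later levels, and could fall under the rule that codes patients with fewer than three levels with the largest CV in their group. For such patients, compute the CV within each agent and combine the results, with the combination rule fixed in advance.

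The cost is one or two degrees of freedom, a few sentences of analysis wording, and a check that the therapy item at T0 records the agent. No added blood samples or visits are needed.

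### The primary ANCOVA adjusts for the drug level at T0, which is not a baseline value of the CV endpoint, and so probably forgoes precision that a pre-T0 CV could bring

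*Protocol article*

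**What the plan says.** Study endpoints defines the outcome from levels recorded at routine visits every four to eight weeks: "A coefficient of variation (%) will be calculated for each patient based on these examination data". Statistical analysis then specifies an ANCOVA of these CVs "with adjustment for immunosuppressive agent level at T0 and all stratification variables considered in the randomization".

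Protection against bias lists the stratification factors, "namely center, gender, and time after transplantation (less than five years or five years or more"). None of them records earlier variability or adherence, and the article names no pre-T0 CV as a covariate anywhere.

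On data sources, the text under Figure 3 says that baseline data are documented retrospectively, that no blood is drawn beyond normal care, and "Necessary data will be extracted retrospectively from patient files and added to the electronic clinical record file during the study".

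The sample size takes no credit for a covariate: "Assuming a two-sided type I error of 5%, a Student’s two-sample t-test will have 80% power under the planning assumptions".

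**The concern.** In an ANCOVA the covariate that usually does most for precision is the endpoint's own value before randomization. Here the outcome describes how much a patient's levels scatter relative to their mean, and the covariate describes where one level lay on one occasion. Two patients with the same T0 level can have very different CVs.

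The planning model in Sample size calculation treats the outcome as a mixture of compliance classes. The mean CV is 0.13 in the very good class and 0.5 in the poor class, each ±0.03. On that picture most of the outcome variance reflects what kind of adherer the patient is. An earlier CV would measure that directly, to the extent that adherence persists; a single concentration is a weaker candidate.

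At stake are the width of the primary confidence interval and the handling of chance imbalance in prior adherence. With 57 per arm, and a variance assumption drawn from six selected patients, extra precision is worth having.

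**Working it through.** **Inputs, all from Sample size calculation**
- Control: "calculated an average coefficient of variation (%) of 0.26, with a standard deviation of 0.15".
- Intervention: "This distribution corresponds to a coefficient of variation (%) of 0.181 with the same standard deviation of 0.15".
- Difference: 0.26 − 0.181 = 0.079.
- Two-sided 5% level, 80% power, 57 per group: "Hence, a total of 114 patients must be recruited for this trial".
- Correlation r between pre-T0 CV and follow-up CV, given the other model terms: not in the article. It is an assumption, shown from 0 to 0.6.

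**Step 1: reproduce the plan.** Normal approximation: n = 2 × (1.960 + 0.842)² × 0.15² / 0.079² = 56.6, so 57 per group. Power at 57 is 0.803 by the normal approximation and 0.796 by the noncentral t. The stated figure holds.

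**Step 2: effect of a covariate.** A covariate with partial correlation r leaves a residual SD of 0.15 × √(1 − r²). Power uses the noncentral t with noncentrality 0.079 / (SD × √(2/57)). The 95% CI half-width is 1.96 × SD × √(2/57). The unadjusted total N giving about the same precision is 114 / (1 − r²).

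| r | residual SD | power at 57 per arm | CI half-width | equivalent N |
|---|---|---|---|---|
| 0 | 0.150 | 0.796 | 0.055 | 114 |
| 0.1 | 0.149 | 0.800 | 0.055 | 115 |
| 0.2 | 0.147 | 0.812 | 0.054 | 119 |
| 0.3 | 0.143 | 0.832 | 0.053 | 125 |
| 0.4 | 0.137 | 0.860 | 0.050 | 136 |
| 0.5 | 0.130 | 0.896 | 0.048 | 152 |
| 0.6 | 0.120 | 0.936 | 0.044 | 178 |

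The table takes 0.15 as the SD before the covariate enters and ignores the degrees of freedom spent on covariate and strata.

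**Step 3: what r might be (illustrative simulation).** It used the 50:25:25 control mixture with CVs of 0.13, 0.28 and 0.50 and a within-class SD of 0.03. The 0.28 is back-solved from the stated mean of 0.26. Assumptions added: log-normal levels around a target unrelated to adherence, and 16 follow-up levels.

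| Correlation with follow-up CV | class fully stable | half the patients redraw their class | no stability |
|---|---|---|---|
| one T0 level | about 0 | about 0 | about 0 |
| pre-T0 CV, 3 levels | 0.61 | 0.30 | 0 |
| pre-T0 CV, 6 levels | 0.72 | 0.36 | 0 |
| pre-T0 CV, 9 levels | 0.76 | 0.38 | 0 |

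The near-zero value for the T0 level follows from the assumption that the target level is unrelated to adherence. It is not a fact from the article.

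**The case against.** **No failure of the plan.** Randomization makes the comparison fair with either covariate, and the sample size uses none. A reader might infer that the wrong covariate biases the result or undermines the 80% power. The documents support neither, and this objection stands in full.

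**The gain is unknown.** At r of 0.2 or less it is negligible (power 0.812 at most), and the r that counts is what remains after center, gender and time since transplantation. This stands.

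**The starting power may be higher.** Taken literally, the 70:30:0 intervention mixture has an SD of about 0.075 to 0.083, not 0.15 (assuming an average-class CV of 0.28 to 0.30 and a within-class SD of 0.03). With SDs of 0.15 and 0.075 to 0.083, the standard error is 0.0222 to 0.0227 and unadjusted power is already about 0.93 to 0.94. The table is therefore conditional on the stated equal SDs.

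**The T0 level may carry information.** A very low level could mark non-adherence. It is also tempting to say that the T0 level mainly encodes which drug a patient takes, but the article names no agents and no drug mix, so that is not supported. The mismatch of scale exists even with a single drug.

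**Shorthand.** The phrase may be condensed wording for the baseline value of the endpoint. That is possible, and Phase I already collects the CV before and after transfer. Even so, the text says level, and an analyst following it would fit the level.

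**Conclusion.** The concern holds as a matter of efficiency. As written, the primary model adjusts for a concentration while the endpoint is a within-patient CV, and nothing else in the model represents earlier variability. The plan probably forgoes precision; it does not lose validity, type I error control or its stated power.

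On the stated planning figures the forgone power runs from nothing worth having (0.80 to 0.81 at r = 0.1 to 0.2) to about 14 percentage points (0.796 to 0.936 at r = 0.6). These gains are measured against a covariate that explains nothing, so they shrink if the T0 level is itself informative. They also rest on adherence being at least partly stable across T0. The mismatch itself is certain from the text; the size of the benefit is not.

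**What to change.** In Statistical analysis, make the covariate the individual CV of routine levels in a prespecified window before T0, for example up to 12 months, or since transplantation if shorter. Compute it with the same formula as the endpoint. It can replace the T0 level or be added to it. Keep the stratification factors. For patients with fewer than three pre-T0 levels, use the pooled mean plus a missing indicator. State how a change of agent within the window is handled. If the current phrase was meant as the baseline CV, say so.

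Fix the wording before outcome data are examined. The Phase I data on CV before and after transfer could give a first estimate of r.

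The cost is extraction of additional routine levels from patient files; no blood sample or visit is added. The main weakness is in patients enrolled close to the three-month post-transplant minimum. At four-to-eight-week spacing they will have about one to three levels, so their baseline is noisy or falls under the missing-data rule. The article does not say how many such patients to expect.

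### Ordinary multivariable logistic regression may give no finite treatment odds ratio for transplant loss in 114 patients, and the stepwise sensitivity model should be replaced by a fixed covariate list

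*Protocol article*

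**What the plan says.** The Statistical analysis section of the protocol article assigns one method to all yes/no secondary endpoints and gives transplant loss as its example: "Secondary dichotomous endpoints (such as transplant loss) will be assessed with multivariate logistic regression models". It lists no covariates for these models and no method for sparse events. Adjustment for every stratification variable (centre, gender, time since transplantation) is stated for the primary analysis of covariance only.

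Study endpoints lists, among other secondary endpoints, "serum creatinine levels, transplant survival, patient survival, acute rejection reactions", and names transplant loss and death separately.

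For the primary endpoint, the planned sensitivity analyses are "multivariate regression models with consideration of additional prognostic factors (modeling after stepwise variable selection"). The article does not say which factors are candidates, what the selection threshold is, or whether treatment must stay in the model.

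The Sample size calculation rests on the coefficient of variation alone: "Hence, a total of 114 patients must be recruited for this trial". The Subjects section excludes patients with signs of acute rejection or a foreseeable need for dialysis. Time points sets the last assessment at 24 months.

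**The concern.** Logistic regression fitted by maximum likelihood has no finite treatment coefficient when one arm has no event. Software then reports a very large coefficient with a meaningless standard error, or fails to converge. Each further covariate adds another way for the fit to separate. A trial sized for a continuous endpoint, in patients selected to be free of imminent graft failure, is where this is likely. The Discussion gives better transplant survival as the long-term goal, so the endpoint closest to that goal could end without a usable effect estimate.

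The stepwise model raises a smaller issue. Choosing covariates from the same data makes the adjustment set depend on the result. The standard errors then ignore the selection, and a sensitivity analysis meant to support the primary result becomes less trustworthy than that result.

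**Working it through.** **Inputs from the protocol article.** 57 patients per arm, 114 in total; two-sided 5%, power 80%; means 0.26 and 0.181, standard deviation 0.15 (Sample size calculation). Follow-up 24 months (Time points). Stratification by centre, gender and time since transplantation (Protection against bias). 17 centres, which is the phase I count.

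**Assumptions.** The article gives no rate of transplant loss, so 24-month control rates of 3%, 5%, 10% and 15% are assumed, with a treatment odds ratio of 0.5.

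**1. The plan's own figure.** n per arm = 2 × (1.960 + 0.842)² × (0.15/0.079)² = 56.6, so 57. This reproduces. The exact t-test power is 79.6% at 57 and 80.3% at 58, which is close enough. No rare endpoint entered this calculation.

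**2. Chance that an arm has no event.** Let p be the control rate and q the intervention rate, with q/(1−q) = 0.5 × p/(1−p). Then P(at least one arm without an event) = 1 − [1 − (1−p)^57] × [1 − (1−q)^57].

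| p | q | Expected events, 57(p+q) | (1−p)^57 | (1−q)^57 | P(at least one empty arm) |
|---|---|---|---|---|---|
| 3% | 1.52% | 2.6 | 0.176 | 0.417 | 52% |
| 5% | 2.56% | 4.3 | 0.054 | 0.228 | 27% |
| 10% | 5.26% | 8.7 | 0.002 | 0.046 | 5% |
| 15% | 8.11% | 13.2 | 0.0001 | 0.008 | 1% |

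First row: 1 − 0.824 × 0.583 = 0.52. In each of these trials no finite treatment odds ratio exists, whatever covariates are added.

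**3. Check by simulated fits** (1,500 trials per setting). With treatment, gender and time since transplantation in the model, the treatment coefficient was non-finite in 51%, 25%, 5% and 1% of trials, in line with step 2. At least one coefficient was non-finite in 71%, 44%, 9% and 1%. If centre were added as 16 indicator terms, some coefficient was non-finite in every trial at every rate. The treatment coefficient itself was then non-finite in 51%, 31%, 5% and 2%.

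**4. Interval width.** Where the treatment coefficient was finite, its 95% interval covered the truth in 94-100% of trials, mostly above 95%. These intervals are wide.

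**5. Power.** For 10% against 5% with 57 per arm, power is 17%; 80% would need 435 per arm.

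**6. Stepwise selection** (simulated, N = 114; candidate numbers and thresholds assumed).
- Treatment forced in, backward selection: coverage of the treatment interval was 93.5-94.7% with 5 to 20 candidates and about 92.5-93% with 30.
- Treatment forced in, forward selection on noise covariates: type I error was 5.3% (20 candidates, p<0.05), 7.7% (20, p<0.157) and 8.5% (30, p<0.157). The Monte Carlo standard error is about 0.6 points.
- Treatment itself open to selection at p<0.05 with 12 other candidates: it was dropped in 19% of trials. When kept, its effect averaged −0.088 against a true −0.079.

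**The case against.** The strongest reply is that the result depends on figures the article does not contain. It gives no event rate, and at 10-15% the problem nearly disappears. Covariate lists and the handling of sparse events are commonly left to an analysis plan, and commoner yes/no endpoints may be unaffected. This limits the point to rare endpoints. It does not remove it, because the article itself chooses the method and names transplant loss as the example.

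Four stronger readings are tempting but not supported:
- *Centre must be in the logistic model, so the fit always breaks down.* Adjustment for centre is stated only for the analysis of covariance, and 17 is the phase I count. Step 2 does not need centre.
- *The intervals will be too narrow.* Finite logistic intervals are wide. For stepwise selection with treatment retained, the loss of coverage is at most 2-3 points.
- *The logistic model ignores unequal follow-up.* The Phase II section requires enrolment at least 14 months before the study ends, which might suggest this. But Time points gives everyone a 24-month assessment, and the sample size section expects little dropout: "We supposed a negligible dropout rate since it is critical that transplant patients receive ongoing care". Differing follow-up is not shown, and the method for the survival endpoints is unstated rather than wrong.
- *A Cox model cures the problem.* An ordinary Cox model also has no finite hazard ratio when an arm has no event.

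It also stands that the stepwise models decide nothing. The conclusion rests on the confidence interval from the analysis of covariance.

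**Conclusion.** The point holds for rare binary endpoints, chiefly transplant loss and death. Followed as written, and if control rates are about 3-5% over 24 months, the plan leaves roughly one trial in two to one in four without a finite treatment odds ratio. At 10% the figure is one in twenty, and at 15% it is negligible. These values rest on the assumed rates and an odds ratio of 0.5. Centre as fixed effects, if used, would make the fit worse.

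Stepwise selection is a lesser weakness. With treatment forced in, type I error is about 5-9%, the upper end needing 20-30 candidates and a lenient threshold. The harm is larger if treatment can be dropped, which the article does not rule out.

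Both matters concern secondary or sensitivity analyses. The primary conclusion is unaffected, so this is a cheap improvement and not a threat to the trial.

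**What to change.** 1. For rare binary endpoints (transplant loss, death), state Firth-penalised logistic regression with treatment and at most the time-since-transplantation stratum, or a risk difference with an exact interval. Do not enter centre as fixed effects.
2. If transplant or patient survival is analysed as time to event, show Kaplan-Meier curves or cumulative incidence and use a Firth-penalised Cox model.
3. For the sensitivity analysis of the primary endpoint, replace stepwise selection with a covariate list fixed before data lock, for example pre-T0 coefficient of variation and age. Treatment and all stratification factors always stay in the model.

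The cost is analysis wording and somewhat less covariate adjustment for secondary endpoints. Recruitment, visits and data collection do not change. No choice of model remedies the low power for rare events, so these results should be reported as estimates with wide intervals.
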